## 4. METHODOLOGY

### 4.1 Description of the Study Design

This study will be an implementation trial to determine the relative effectiveness of two methods for delivering PrEP to barmaids in Dar es Salaam, a population group at high risk for HIV acquisition. The drug provided will be Tenofovir disoproxil fumarate 300 mg and emtricitabine 200 mg, prescribed to be taken orally as a pill once per day. This will be a single-site study and will be collaboratively be conducted by Heidelberg University, the Muhimbili University of Allied Health Sciences (MUHAS) Management and Development for Health (MDH). Implementation of this study will be conducted by MUHAS and MDH, with no clinical care or oversight roles for Heidelberg personnel. Heidelberg personnel will have access to de-identified data only for evaluation purposes, and no contact with human subjects.

Tanzanian research team will visit barmaids in the Ubungu municipal council of Dar es Salaam (formerly part of Kinondoni district, where the piloting was done), and invite them to participate in HIV testing and counseling (HTC). Those who agree to participate will receive

standard HTC procedures as laid out on in the current national Tanzanian guidelines [24]. Standard HTC includes pre-test counselling, a finger-prick based, a rapid HIV test (followed by a second confirmatory test with a second test type should the first test prove positive), and then a post-test counselling. Individuals who test positive for HIV will be linked to HIV care and treatment services at a local HIV Care and Treatment Clinic (CTC), using a routine linkage process from community to facility. At the CTC, individuals will get a confirmatory HIV test and will then be offered immediate antiretroviral therapy (ART) based on current national guidelines for the management of HIV and AIDS [24]. All individuals who test negative for HIV will be actively linked to a PrEP intervention as per the Tanzania National PrEP Framework [25].

The study will involve two serial randomizations. The first randomization will occur at the bar level where barmaids working in a given bar will be offered the ability to initiate PrEP either: (1) at the bar in which the barmaid is working (“workplace-based”), and where they will be recruited to the study by Community based HIV care providers; or (2) at a selected public healthcare clinic already have trained health care workers trained on PrEP and already providing PrEP, as well as providing HIV treatment and care services (“facility-based”). The second randomization will be at the individual level where enrolled PrEP clients will be randomized to either: (A) being supported by an omni-channel PrEP Champion or (B) not being supported by an omni-channel PrEP Champion.

We will identify four facilities to participate in this PrEP provision trial. The criteria for selection will include: (i) existence of HIV care and treatment services; (ii) having a well-established ARV supply chain; (iii) having trained health care providers on how to offer PrEP; and (iv) provide HIV prevention services including condom distribution and comprehensive Positive Health Dignity Prevention (PHDP) services [24]. At each selected facility, we will identify a two well-trained HIV nurse counselors and one ART trained clinician, per WHO recommendations [26] and National PrEP Framework [25]. These staff will be paid for the overtime work they will undertake in supporting this study. The clinicians will be responsible for taking a clinical history and prescribing PrEP. The nurse counsellors will be responsible for providing adherence counselling, issuing PrEP pills and following-up clients for PrEP refills.

### **Randomization 1: PrEP delivery method**

We will randomly assign bars to one of two PrEP delivery groups: facility-based or workplace-based. All women enrolled onto PrEP from each bar will be assigned to their bars' study group, i.e. this is a cluster-randomized design. Bar-level clusters will be used to avoid study contamination and ensure smooth study operationalization.

**Group 1a. Facility-based PrEP delivery:** All HIV-negative participants in facility-based group bars will be offered the opportunity to initiate PrEP. If they agree to participate, they will be introduced to an assigned peer navigator. The peer navigator will arrange a time to escort the barmaid to their preferred health facility (from the list prepared by the study team) for PrEP services. At the facility, they will be started on emtricitabine/tenofovir disoproxil, with direct observation of the first dose. The study team will actively follow-up the clients to discontinue the participant from PrEP in case they show any signs of side effects. This practice of immediate initiation of treatment followed by discontinuation of treatment among participants with contraindications is comparable to Tanzanian's current guidelines for immediate initiation of ART in HIV-positive patients and PrEP implementation framework.

At the enrolment visit, participants will be scheduled for regular follow-up visits at the facility to monitor medication adherence and safety, once every 2 months, and to receive a PrEP prescription refill on monthly basis.. These visits will include HIV testing, creatinine levels, screening and treatment for STIs as required, and adherence counselling. All these services are standard of care for monitoring patients on treatment and fulfill monitoring requirements in national PrEP and HIV treatment guidelines [24].

**Group 1b. Workplace-based PrEP delivery:** HIV-negative participants in workplace-based group bars will be offered the opportunity to initiate PrEP at the bar immediately. If they agree to participate, they will be started on emtricitabine/tenofovir disoproxil, with direct observation of the first dose. This initiation will be conducted by study healthcare staff who are allowed to prescribe ART as per Tanzania national policy. Again, should test results subsequently show that participants meet for side effects or other exclusion criteria, the study team will actively follow up to discontinue the participant from PrEP. All subsequent visits will be as in the facility-based group but carried out at the workplace with the assistance of the Community based HIV care providers. The Community based HIV care providers will provide refills; conduct monitoring,

and record inconveniences encountered – since this is an important part of the feasibility assessment for this mode of delivery.

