## **2.4 Potential Risks and Benefits**

### **2.4.1 KNOWN POTENTIAL RISKS**

One risk for emtricitabine/tenofovir disoproxil taken as PrEP is that if someone is HIV-positive they may be at increased risk of developing resistance to the two active drugs. To avoid this we will test individuals for HIV at baseline, month 2 and month 4 during the trial. We will also conduct a detailed assessment of possible acute viral infection based on clinical symptoms; where such symptoms are present initiation will be delayed by one month and a second HIV test performed. Possible adverse reactions to emtricitabine/tenofovir disoproxil noted in its package insert include lactic acidosis/severe hepatomegaly with steatosis, exacerbation of Hepatitis B infection, onset or worsening of renal impairment and loss of bone mineral density. Following the WHO PrEP guidelines [17] Hepatitis B surface antigens will be clinically tested at baseline, with only individuals testing negative considered eligible for the trial. Individuals testing positive will be linked to specialized clinics for further testing and assessed for treatment. Serum creatinine levels will also be assessed at baseline to identify pre-existing renal disease, and at endline (6months). Only individuals with serum creatinine levels less than 60ml/min will be considered eligible to enroll in the trial. A range of other adverse reactions have been seen in clinical trials of emtricitabine/tenofovir disoproxil, including most commonly diarrhea, nausea, fatigue, headache, dizziness, depression, insomnia, abnormal dreams, and rash.

All of these risks are offset by the potential protection emtricitabine/tenofovir disoproxil provides against HIV acquisition in this very high-risk population of young women, who self-report very high levels of sexual activity with multiple partners, including a substantial minority reporting sex in exchange for money or goods. In Tanzania some health care providers from some health facilities have been trained on how to offer PrEP to customers.

Therefore, in this study some selected facilities with trained health care providers on how to offer PrEP in Tanzania will be selected to participate in this study.. Therefore, we will identify four facilities which provide PrEP and select some trained health care providers on PrEP to participate in this study.

---

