### **5.4 Participant Withdrawal or termination**

#### **5.4.1 Reasons for Withdrawal or Termination**

Participants are free to withdraw from participation in the study at any time upon their requests and on their will without being forced or intimidated. The participants will be given clear explanation on the study, process and all procedures that will be done. The issue of withdrawal will be explained clearly that they can stop to participate in the study at any time and that their

withdrawal from the study will have no influence on how they will be treated or handled afterwards.

An investigator may terminate participation in the study (i.e. stop provision of PrEP) if:

- A participant tests positive for HIV
- A participants' renal function drops abnormally low
- Any clinical adverse event (AE), laboratory abnormality, or other medical condition or situation occurs such that continued participation in the study would not be in the best interest of a participant
- A participant ceases to work as a barmaid in Dar es Salaam

Apart from the above reasons for withdrawal or termination of participation in the study, the informed consent has a component that explains about stopping participation and that it will not impose any penalty to the participant.

---

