### **6.1.8 DOSE ADJUSTMENTS/MODIFICATIONS/DELAYS**

None

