### **7.3.3 FOLLOW-UP**

#### **Refill Visit 1 (Visit 1 Day 30 +/- 7; Month 1)**

- Provide additional 28-days (1 month) supply of medication to the participant
- Check on adverse effects
- Adherence Counselling
- Test for HIV

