## **10.3 Protocol Deviations**

A protocol deviation is any noncompliance with the clinical trial protocol, GCP, or MOP requirements. The noncompliance may be either on the part of the participant, the investigator, or the study site staff. As a result of deviations, corrective actions are to be developed by the site and implemented promptly. These practices are consistent with ICH E6:

- 4.5 Compliance with Protocol, sections 4.5.1, 4.5.2, and 4.5.3
- 5.1 Quality Assurance and Quality Control, section 5.1.1
- 5.20 Noncompliance, sections 5.20.1, and 5.20.2.

It is the responsibility of the site to use continuous vigilance to identify and report deviations within 3 working days of identification of the protocol deviation, or within 7 working days of the scheduled protocol-required activity. Protocol deviations must be sent to the local IRB per their guidelines. The Tanzanian site PI and Tanzanian healthcare providers are responsible for knowing and adhering to their IRB requirements.

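### Section 4.1 (Group 1a) orders PrEP stopped for any side effect, which is broader than its own rationale and inconsistent with the best-interest criterion in section 5.4.1

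*Protocol*

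**What the plan says.** The protocol describes when staff take a woman off PrEP in three places.

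- **Section 4.1, Group 1a (facility-based).** The study team will follow clients up to "discontinue the participant from PrEP in case they show any signs of side effects". The next sentence likens this to national practice of immediate initiation "followed by discontinuation of treatment among participants with contraindications".
- **Section 4.1, Group 1b (workplace-based).** The clause reads "Again, should test results subsequently show that participants meet for side effects or other exclusion criteria", after which the team will actively follow up to stop PrEP.
- **Section 5.4.1 (no arm named).** An investigator may stop supplying PrEP on several grounds. They include a positive HIV test, an abnormal fall in renal function, and any adverse event, laboratory abnormality or other condition "such that continued participation in the study would not be in the best interest of a participant".

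Section 2.4.1 describes the reactions seen in trials of the drug, "including most commonly diarrhea, nausea, fatigue, headache, dizziness, depression, insomnia, abnormal dreams, and rash". At the month 1, 3 and 5 refill visits (section 7.3.3), staff hand over a further 28-day supply and carry out the item "Check on adverse effects". No instruction to stop is attached.

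**The concern.** The Group 1a sentence is an operative stopping instruction, and as written it is unconditional. Any sign of a side effect is enough, whatever its severity or cause. Section 5.4.1 deals with the same action and makes it a matter of clinical judgement. A clinician who sees a facility-arm woman with mild nausea at month 1 is told to stop by one section and to weigh her interest by the other.

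The main stake is participant welfare. The trial enrols women because they are at high risk of acquiring HIV, and a literal reading withdraws their protection for complaints that the protocol itself calls common. Stopping is also closely tied to what the trial measures: month-6 urine TDF (primary endpoint 2) and refill counts (secondary endpoint 1). The rule that produces stops should therefore be stated once and clearly.

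**Working it through.** No arithmetic applies: the protocol gives no side-effect rate or stop rate. The check sets the rules side by side and then applies them to specific cases.

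**Step 1. The rules compared**

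| Feature | 4.1 Group 1a | 4.1 Group 1b | 5.4.1 |
|---|---|---|---|
| Force | team *will* follow up to stop | team *will* follow up to stop | investigator *may* stop |
| Who acts or decides | study team | study team | investigator |
| Trigger | any sign of a side effect | later test results showing side effects or exclusion criteria (clause garbled) | adverse event, laboratory abnormality or other condition that makes continuing contrary to her interest; also HIV or low renal function |
| Severity threshold | none | none stated | best-interest judgement |

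Group 1a and section 5.4.1 differ on force, decision-maker and threshold.

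**Step 2. Group 1a against its own rationale**

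The trigger sentence speaks of side effects. The sentence that justifies it speaks of "followed by discontinuation of treatment among participants with contraindications". Nausea, headache and fatigue are not among the exclusion criteria in section 5.2, so the instruction reaches well beyond the reason given for it.

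**Step 3. Cases**

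- *Mild nausea at month 1.* Group 1a, read literally: stop. Group 1a's rationale: continue, since nausea is not a listed exclusion. Group 1b: unclear, because nausea is not a test result. Section 5.4.1: continue unless the investigator judges that stopping serves her. The rules diverge.
- *Creatinine result below the section 5.2 limit, returned after the first dose.* Group 1a's trigger does not mention test results, and only its rationale covers this. Group 1b: stop. Section 5.4.1: may stop.
- *Positive hepatitis B surface antigen returned after the first dose.* Group 1b: stop, since it is an exclusion criterion. Section 5.4.1 does not name hepatitis B, so it is reached only through the general item, and only as something the investigator may do.
- *Severe adverse event.* Every reading leads to a stop or readily permits one.

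**Step 4. Which text is the outlier**

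The rest of the protocol treats side effects as events to record and manage. Section 8.2.1 defines mild events as needing little or no treatment. Section 8.3 has adverse events followed to resolution and changes in severity documented. Section 4.2 surveys side effects at midline and endline, and section 4.3.3 counts the women who report them. Section 7.3.3 pairs the adverse-effect check with a new supply. None of these makes a side effect an automatic stop. The Group 1a sentence stands alone.

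**The case against.** The best defence is that context supplies the meaning. Section 4.1 is a design overview about starting PrEP the same day and recalling women later. Its next sentence mentions contraindications, and Group 1b opens by saying the same again. Section 5.4.1 is the more specific operational text, and clinicians will use judgement. This is a fair account of what was probably meant, and it keeps the point minor. It does not cure the sentence, because a stopping instruction should not depend on staff guessing that it means something narrower.

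Four stronger readings are tempting, and the documents do not support them.

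1. *No action is compliant.* Section 10.3 says "A protocol deviation is any noncompliance with the clinical trial protocol, GCP, or MOP requirements", so a reader might infer that both keeping and stopping a woman with mild nausea would be deviations. Keeping her does depart from the literal Group 1a text. Stopping her need not breach section 5.4.1, which is a permissive list, does not say it is exhaustive, and allows a stop when the investigator judges it in her interest.
2. *Nothing lies between continuing and stopping.* Section 6.1.8 ("DOSE ADJUSTMENTS/MODIFICATIONS/DELAYS") says there are none. That rules out changing the dose, not managing the event. Sections 8.2.1 and 8.3 provide for treatment and follow-up.
3. *The wording biases the comparison between arms.* Group 1b also names side effects, refers back to Group 1a, and says later visits run as in the facility group. One rule was probably intended. Different stopping by arm would require staff in this unblinded trial to follow their own paragraph to the letter, and neither size nor direction follows from the text.
4. *The effect can be sized from the planned arm of 80.* One woman moving from 80 ng/mL to zero shifts a raw arm mean by 80/80 = 1 ng/mL. That is the weight of any stop for any reason, on a scale the planned log-transformed test does not use. Nor is the zero automatic: section 5.4.2 keeps women who stop PrEP but remain otherwise eligible in follow-up.

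**Conclusion.** Wrong as written, minor. The Group 1a sentence is an unconditional stop for any side effect. It is broader than the rationale beside it and inconsistent with the investigator-judged criterion in section 5.4.1, and no other section reconciles them. The practical harm is that a literal reading takes women at high risk of HIV off PrEP for mild, common reactions. How many would be affected cannot be stated, since the protocol gives neither a side-effect rate nor a stop rate. Group 1b's wording is garbled and should be repaired at the same time, but an intended difference between arms is not established and no bias in the endpoints is claimed. The conclusion assumes only that staff may act on the sentence as it stands.

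**What to change.** Replace the stop sentences in Group 1a and Group 1b with one identical sentence, for example:

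> *The study team will actively follow up to discontinue PrEP in any participant whose subsequent test results show an exclusion criterion or contraindication (HIV, HBsAg, renal function); other adverse events will lead to discontinuation only when the investigator judges under section 5.4.1 that continuing is not in her best interest.*

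A bare cross-reference to section 5.4.1 would not be enough. It would drop the duty to recall women whose later results show an exclusion criterion. Section 5.4.1 says only that the investigator may act and does not name hepatitis B, while section 7.2 sends both the hepatitis B and creatinine samples to the laboratory.

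The cost is two sentences in section 4.1. No participants, visits, tests or changes to the analysis are needed.

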## **5.2 Participant Exclusion Criteria**

- Report past diagnosis of renal disease
- Report past diagnosis of diabetes
- Report past diagnosis of hypertension
- Report current use of nephrotoxic medication
- Report flu-like symptoms that may represent acute HIV infection
- Report currently taking any of the following medications:
  - Any medicine containing emtricitabine or tenofovir disoproxil fumarate
  - Any medicine containing tenofovir alafenamide
  - Any medicine containing lamivudine
  - Adefovir
  - Didanosine
  - Atazanavir
  - Ledipasvir with sofosbuvir
  - Darunavir
  - Lopinavir with ritonavir
- Report bone pain or other bone problems
- Test positive for HIV or be unwilling to complete HIV counselling and testing.
- Test abnormally low for renal function using a serum creatinine test (<60ml/min).

- Test positive for Hepatitis B based on a hepatitis B surface antigen (HBsAg) test.

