### 7.3. Study Schedule

#### 7.3.1 SCREENING

##### Recruitment and Screening visit

- Recruitment of barmaids for screening and PrEP intervention
- Obtain informed consent of potential participant verified by signature on screening informed consent form.
- Conduct screening questionnaire.
- Obtain demographic information and medical, medication, alcohol and tobacco use history.
- Review medical history to determine eligibility based on inclusion/exclusion criteria.
- Review medications history to determine eligibility based on inclusion/exclusion criteria.
- Perform medical examinations needed to determine eligibility based on inclusion/exclusion criteria. Specifically we will perform:
  - A point-of-care HIV test as part of standard HIV counselling and testing;
  - A point-of-care Hepatitis B surface antigen (HBsAg);and
  - Blood sample collection for a local, laboratory-based test of serum creatinine and syphilis.
- Schedule study visits for participants who are eligible and available for the duration of the study.

- The screening visit will require between 1.5 and 2 hours to complete

---

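### Section 2.4.1 prints the renal eligibility limit backwards, and Section 4.1 allows the first dose before a laboratory result that Sections 5.2 and 7.3.2 treat as an entry condition

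*Protocol*

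**What the plan says.** **Renal limit.** Section 2.4.1 states: "Only individuals with serum creatinine levels less than 60ml/min will be considered eligible to enroll in the trial". Section 5.2 lists as an exclusion: "Test abnormally low for renal function using a serum creatinine test (<60ml/min". Section 5.4.1 lets the investigator stop PrEP if renal function becomes abnormally low.

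**Hepatitis B.** Section 2.4.1 states: "Hepatitis B surface antigens will be clinically tested at baseline, with only individuals testing negative considered eligible for the trial". Section 5.2 excludes a positive HBsAg.

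**Order of events.** Section 7.3.1 has staff, at screening, "Perform medical examinations needed to determine eligibility based on inclusion/exclusion criteria", and one item under that heading is "Blood sample collection for a local, laboratory-based test of serum creatinine and syphilis". Section 7.3.2 lists a check of the inclusion and exclusion criteria ahead of the observed first dose.

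**First dose.** Section 4.1, Group 1b: "HIV-negative participants in workplace-based group bars will be offered the opportunity to initiate PrEP at the bar immediately". It then provides for discontinuation "should test results subsequently show that participants meet for side effects or other exclusion criteria". Group 1a describes its own procedure as "This practice of immediate initiation of treatment followed by discontinuation of treatment among participants with contraindications" and calls it comparable to national practice for ART and PrEP.

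**Where tests are run.** Creatinine goes to the laboratory in Sections 7.1.1, 7.2 and 7.3.1. HBsAg is point-of-care in Sections 7.1.1, 7.3.1 and 7.3.4, but Section 7.2 sends it to the laboratory.

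**The concern.** Section 2.4.1 names renal impairment and hepatitis B exacerbation as risks of the study drug. The same paragraph then gives the renal threshold in the wrong direction. Section 11.4.2 points back to 2.4.1 for the adverse effects to be explained at consent, so the error sits in text that staff will consult.

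The second problem is operational. Take an HIV-negative woman whose creatinine result is still at the laboratory. Staff following Group 1b would give her the first tablet. Staff following Sections 5.2 and 7.3.2 would wait. Both cannot be right, and a statistical analysis plan cannot settle it, because it is a dosing rule. What is at stake is dosing women whose renal status, and on one reading hepatitis B status, is unknown, and possibly doing so differently between staff or arms.

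**Working it through.** No plan figure needs reproducing; the check is a comparison of sections.

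1. **Direction of the renal limit.** Section 2.4.1 admits women below 60 ml/min; Section 5.2 excludes women below 60 ml/min. Section 5.4.1 treats falling renal function as a reason to stop, which agrees with 5.2. The error is therefore in 2.4.1. The sentence also gives a serum creatinine level in ml/min, which is a unit of clearance.

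2. **Which exclusions depend on a test.** Section 5.2 has three: HIV, renal function and HBsAg. HIV is a rapid test, read on the spot. Syphilis is tested but is not an exclusion. So the only results that can show an exclusion criterion after dosing are creatinine and, depending on where it is run, HBsAg.

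3. **Creatinine.** Every section that names the test site makes it a laboratory test. Group 1b's immediate start, with a stop on later results, therefore conflicts with Sections 5.2, 7.3.1 and 7.3.2.

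4. **HBsAg.** Under Sections 7.1.1, 7.3.1 and 7.3.4 it is point-of-care, and 7.1.1 has rapid results given when the test is done, so it can be known before dosing. Under Section 7.2 it cannot be known on the same day. The conflict for HBsAg exists only because of 7.2.

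5. **Does a separate baseline visit remove the conflict?** Sections 7.3.1 and 7.3.2 describe two visits, and results could be back by the second. No interval is stated, however, and Group 1b expressly provides for exclusion results arriving after the start.

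6. **Facility arm.** The stop rule in Group 1a names only side effects. The start-then-stop reading rests on the following sentence about contraindications, so the evidence is weaker there than in Group 1b.

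7. **Later safeguard.** The schedule in Section 7.3.6 shows creatinine and HBsAg at screening and then only at the final visit. Group 1a mentions creatinine at follow-up visits, but the schedule does not carry this.

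8. **Analysis sets.** Section 10.5.2 defines the endpoint 2 set (MITT) by the observed Day 0 pill and the endpoint 1 set (ITT) by being found eligible. A woman dosed and then found ineligible is in the MITT set but, read strictly, outside the ITT set.

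9. **Scale of one such woman.** Endpoint 2 plans 40 + 40 = 80 per arm (Section 9.4.1), so she is 1/80 = 1.25% of an arm. For endpoint 1 (Section 9.3: 320 workplace, 800 facility) she is 1/320 = 0.31 or 1/800 = 0.13 percentage points, against a planned difference of 25 − 10 = 15 points.

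**The case against.** The best defence is that start-then-stop is deliberate. Group 1a ties it to national ART and PrEP practice, and Sections 3 and 4.3.1 make immediate on-site initiation the intervention under test. Requiring a creatinine result before every first dose would remove the same-day start. That stands: it argues against imposing a wait, and whether national rules require the result first cannot be judged from this document. It does not reconcile Section 4.1 with Sections 5.2 and 7.3.2, which still say something else.

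It can also be said that 2.4.1 is a slip in narrative text and that 5.2 is the operative list. That is correct. A reader might infer that women with poor renal function would be enrolled; the protocol does not support that, because 5.2 and 5.4.1 point the right way.

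A reader might also infer that it is unclear whether a woman dosed and then found ineligible belongs in endpoint 2. It is not. Section 10.5.2 takes everyone observed to start, and the MITT sentence in Section 10.5 agrees; the eligibility wording there belongs to the ITT set. Nor does the zero rule matter much for her. Once taken off the drug she should have about no tenofovir at month 6 whether measured or imputed, since Section 9.3 says there is no other access to PrEP.

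**Conclusion.** The point holds in two parts. The renal limit in Section 2.4.1 is wrong as written and contradicts 5.2; this needs no assumption. The first-dose rule is contradictory, explicitly for the workplace arm and less so for the facility arm. It is firm for creatinine and depends on Section 7.2 for HBsAg.

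The importance lies in eligibility and safety, not in power. A loss of power for endpoint 2 might be inferred if such women are scored zero, but the protocol gives neither the share with an excluding result nor the value to be used for the log of zero. Any power figure would rest on assumed inputs, so none is claimed. That the MITT set is not strictly contained in the ITT set is a minor consistency point for the SAP.

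**What to change.** 1. In Section 2.4.1, state that renal function (creatinine clearance) of 60 ml/min or more is eligible. This costs nothing.
2. Align Section 7.2 with 7.1.1, 7.3.1 and 7.3.4: HBsAg is done at point of care and must be negative before the first dose, in both arms. Same-day starts are kept.
3. State one creatinine rule for both arms. The low-cost version amends Sections 5.2 and 7.3.2 to allow the first dose once screening blood has been drawn, with prompt discontinuation if that sample shows less than 60 ml/min. This keeps the contrast under test. Its price is that a few women take the drug briefly with renal function unknown. If, purely for illustration, 0.5% to 3% of the 160 initiators had an excluding result, that would be 160 × 0.005 = 0.8 to 160 × 0.03 = 4.8 women. The alternative, result in hand before dosing, avoids that exposure but gives up some same-day starts.
4. In the SAP, note how women dosed and then found ineligible are treated in each set. Removing them from both sets is not recommended: endpoint 1 is defined on women offered PrEP (Section 4.3.1) and sized on HIV-negative screened women (Section 9.3).

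No new samples are needed, because the screening blood is already drawn in both arms.
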